## Qualitative methods

The sample size for the qualitative component has been determined by the principle of saturation (62); we anticipate that 15 post-intervention interviews will need to be conducted (63). Participants will have the opportunity to consent to the qualitative interview during the initial informed consent discussion at the time of recruitment. The interview would be conducted virtually or in person. We will invite participants who completed the trial and participants who chose to withdraw from the study. Views of the d-DBT intervention, treatment target preferences, and experiences of assessment schedules will be obtained in individual, semi-structured interviews at intervention completion. Interview data will also be collected on usability of the virtual platform, experiences participating remotely/technical experience, overall perception of the program, and barriers/facilitators to participation. An interview guide will be developed from existing literature, together with feedback from the youth advisory group, and will consist of key questions with prompts to enquire further. All interview data will be transcribed verbatim. Data will be analyzed using the five stages of framework analysis (64). Rigor will be ensured by maintaining an audit trail to foster dependability of the process. Confirmability and credibility will be assured by a team approach to data analysis and discussion of the emerging themes. Consensus of the final theoretical framework, reflexivity, and the impact of the researchers on recruitment, data collection and analysis will also be considered (65).

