## Outcome Assessments

**Measures/Assessment Tools:** Demographic and medical comorbidity assessments, and current medication use will be gathered at baseline. Measures will be completed at study entry and repeated immediately post-intervention at 8-weeks. Clinician rated assessments will be completed with a trained research assistant. Any changes to medication will be recorded at intervention completion. Psychiatric diagnoses will be confirmed using the Structured Clinical Interview for DSM-5 (SCID-5) and Structured Interview for Psychosis-risk Syndromes (SIPS) at baseline. Clinical assessments will be completed at baseline and 8-weeks.

Primary outcomes:

1. Feasibility outcomes will include recruitment (60 participants), retention, and completeness of modules. Completeness of modules will be assessed using a brief survey after every module and participants will receive weekly virtual check ins to help with trouble shooting and enhance engagement. Participants’ ability to complete the clinical assessment schedule will also serve as a feasibility indicator.
2. Acceptability will be informed by the Client Satisfaction Questionnaire (CSQ-8) (66). Semi-structured interviews at the end of the intervention will also provide feasibility and acceptability data.
3. System Usability Scale (SUS) (67) - assesses whether the intervention is serviceable for its intended purpose. The SUS is a reliable tool for measuring the usability. It consists of a 10-item questionnaire with five response options for respondents; from Strongly agree to Strongly disagree.

Secondary Outcomes:

1. Global Functioning: Social and Role Scales (68).
2. Psychosis spectrum symptoms: SIPS (69); PRIME-Revised (70)
3. Mood and anxiety: The State-Trait Anxiety Inventory (71), Calgary Depression Scale for Schizophrenia (72).
4. Emotion Regulation: Brief Difficulties in Emotion Regulation Scale (DERS-16) (73).
5. Substance Use: Adolescent Alcohol and Drug Involvement Scale The Timeline Follow Back (TLFB) method for measuring quantity of cannabis, alcohol, and tobacco use in the past 7 days (74); The Cannabis Use Disorders Identification Test-Revised (CUDIT-R) (75);Daily Sessions, Frequency, Age of Onset and Quantity of Cannabis Use Inventory (DFAQ-CU) (76)
6. Borderline personality dimensions: BSL-23 (77).
7. Resiliency: Connor-Davidson Resilience Scale; CD-RISC (78).
8. Suicidal ideation: Columbia-Suicide Severity Rating Scale (79).

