Research personnel will contact participants according to their preferred mode of communication (email, telephone, SMS text), which will be recorded in the pre-screening/subject log. In the case of text messaging, personnel will only contact participants to schedule or remind participants of upcoming appointments.

All patients will be given the option to participate. Participation in the study is voluntary. The decision to participate will not affect patients’ receipt of treatment or clinical services. Participants will be informed that they have the option of terminating their participation at any time, without consequence and that no new data will be collected on them.

Participants will be recruited through the Slaight Centre for Youth in Transition’s centralized recruitment process. All subjects will be pre-screened with the Slaight REB approved “pre-screen form” that is implemented across all SFCYT studies to allow for alignment and data sharing and recruitment; this data will be entered into a password protected and restricted pre-screen tracking database. We conduct case review meetings twice a week to review recruitment and to identify new patients who may be eligible for research studies. Our centralized recruitment strategy allows us to ‘triage’ and ‘group’ participants into non-competing research studies to encourage referrals among PIs.

Recruitment will also be enhanced by the Toronto Adolescent and Youth (TAY) Cohort study (PI; [name]) that is recruiting 3000 youth, and emerging adults, aged 11-24 years over 5-years. The TAY study offers rich phenotypic data and aims to investigate mechanisms of disease in young people presenting to mental health services. We expect to identify many individuals with CHR from the TAY Cohort study, where to date almost 50% of participants demonstrate clinically significant levels of psychosis spectrum symptoms.

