## Participant Withdrawal Criteria

Participants are advised in the consent form that they are free to withdraw from the study at any time without prejudice and may be withdrawn at the Investigators discretion.

The study participation will also be terminated should participants develop or are found to have any condition that might compromise safety (e.g., unstable vitals). Other reasons for withdrawing individual participants from the study may include one of the following:

- Major protocol violation
- Participant lost to follow-up.
- Withdrawal of consent
- Any participant may be discontinued from the study at the discretion of the investigators if it is deemed to be in the best interest of the participant.

The reason for participant discontinuation or withdrawal from the study will be recorded within the participant’s research record, and/or legal health record.

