## Statistical Methods

Data will be analyzed principally using descriptive statistics to assess rates of recruitment, retention, intervention fidelity, engagement, and treatment response. Distributional characteristics of the outcome measures will be assessed for ceiling and floor effects and rates and patterns of missing values. Exploratory trial outcomes including impact of d-DBT on emotional regulation, psychiatric symptoms and functioning will be analyzed using (generalized) linear mixed-effects models with time (baseline, post-treatment), group (d-DBT vs control), time by treatment interaction as the primary predictor. The model will also include covariates to account for pre-treatment clinical characteristics and/or key demographics. The model form will be determined by the distribution features of the outcomes of interest (e.g, continuous, binary or count-type). The efficacy outcome will be impact of d-DBT on functioning, via the Global Functioning: Social and Role Scales. Our prior work with youth has informed us that functioning is more relevant to them than symptom severity (91). Given the small sample size, appropriate to a feasibility trial, we will also calculate point and confidence estimate of effect sizes (Cohen’s *d*) Effect sizes will help with the estimation of the sample size needed for a larger scale confirmatory randomized control trial in the future. Both ITT analysis and per-protocol/completers-only analysis will be conducted to gain insight of estimated efficacy of different subgroups of participants. Full information maximum likelihood approach will be adopted to deal with missing data under the missing-at-random assumption. Diagnostic analysis will be conducted to evaluate the soundness of the statistical assumptions carried by the methods. While the analytic approach can be seen as too complex for the small sample size, it will offer guidance for the analysis plan of the full-scaled trial.

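### The protocol plans interviews with people who have withdrawn, yet has participants told that stopping ends all new data collection

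*Protocol*

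**What the plan says.** - **Assurance to participants** (Protocol, Participant Recruitment and Screening). The right to stop is to be explained in these terms: "terminating their participation at any time, without consequence and that no new data will be collected on them".
- **Who is interviewed** (Protocol, Qualitative methods). "We will invite participants who completed the trial and participants who chose to withdraw from the study". On consent: "Participants will have the opportunity to consent to the qualitative interview during the initial informed consent discussion at the time of recruitment". On timing, views "will be obtained in individual, semi-structured interviews at intervention completion".
- **Role of the interviews** (Protocol, Outcome Assessments). Under the primary outcomes: "Semi-structured interviews at the end of the intervention will also provide feasibility and acceptability data".
- **Other acceptability instruments** (Protocol, Schedule of Events). The CSQ-8, the SUS and the interview are each marked only at the follow-up visit.
- **Withdrawal** (Protocol, Participant Withdrawal Criteria). The section speaks of leaving the study. Its list of possible reasons includes "Major protocol violation", loss to follow-up and withdrawal of consent. Stopping the programme while staying in the study is not described.
- **Analysis** (Protocol, Statistical Methods). "Both ITT analysis and per-protocol/completers-only analysis will be conducted", with full information maximum likelihood (FIML) under missing-at-random for missing outcomes.

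**The concern.** The two statements about people who leave give staff opposite instructions. One closes data collection when a participant stops; the other plans a further data collection from some of the same people. The interviews belong to a primary outcome of a feasibility trial, so the choice is not a side matter.

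At stake is either the evidence or the assurance. People who leave are well placed to say what made the programme hard to accept, and the protocol evidently wants to hear from them. If they cannot be approached, satisfaction, usability and interview findings describe stayers only. If they are approached, participants were told something that turned out not to be true.

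**Working it through.** The core of this point is a comparison of texts. Arithmetic enters only to size it.

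**1. Do the statements cover the same people?** The assurance concerns anyone who terminates participation. The interview plan names people who withdrew by choice. The second group lies within the first.

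**2. Is an interview new data?** Yes. It is to be transcribed, analysed and reported as outcome evidence. It is set at intervention completion, so for someone who has already left the study it comes after the withdrawal.

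**3. Does any text reconcile them?** Interview consent is offered at recruitment, but the protocol does not say that this consent survives withdrawal, and the assurance carries no exception for the interview. The withdrawal section does not address the question.

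**4. What follows under each reading?**

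| If staff follow | Interview, CSQ-8, SUS from people who withdrew | Consequence |
| --- | --- | --- |
| the assurance | none, as all three fall at follow-up | this evidence describes stayers only |
| the interview plan | interview possible | what participants were told is broken |

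Under either reading, attendance, post-module surveys and the weekly check-ins up to withdrawal are kept.

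**5. How many people?** Inputs: 60 participants, 30 per arm, about 20% dropout (Overall Design; Sample Size and Power for quantitative methods).

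- Overall: 0.20 × 60 = 12.
- d-DBT arm, assuming equal loss: 0.20 × 30 = 6.

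These are upper figures at that rate, because dropout also includes people lost to follow-up, who could not be interviewed anyway. Participant Compliance Monitoring quotes 26% dropout for digital interventions, but also says a human component cuts attrition by more than half. That would mean below 0.5 × 26% = 13%, or fewer than 0.13 × 30 = 3.9 people in the d-DBT arm. The 26% should therefore not be applied directly to this trial.

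**6. Does it affect the efficacy figures?** The stated 95% margin of ±0.57 SD reproduces with 24 per arm: 1.96 × √(2/24) = 0.566. That is 48 of 60 with a week-8 outcome, so this figure already allows for leavers giving none. FIML still uses their baseline data. With r the baseline to week-8 correlation (assumed 0.5), the variance of mean change per arm in SD units is (1 − r²)/24 + (1 − r)²/30 = 0.03125 + 0.00833 = 0.03958. The margin is 1.96 × √(2 × 0.03958) = 0.551, against 0.566 for completers only and 0.506 with no loss. Leavers thus stay in the model, though they add little.

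The remaining issue is the assumption itself. With one post-baseline visit there is no outcome on leavers to set against missing-at-random. If the between-arm difference among leavers departs from its prediction by D SD, the bias is about 0.2 × D. The documents give no value for D.

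**The case against.** **The interview is voluntary and has its own consent.** People are invited, not required, and may agree at entry. The consent form is not at hand and might contain wording that reconciles the two statements. This limits the point but does not remove it: the protocol states what participants will be told, without qualification, and should not depend on another document to correct it.

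**Leavers are not silent on acceptability.** Specific Aim 2 counts attendance as acceptability evidence, a survey follows each module, and the weekly check-ins explore barriers. Attrition is itself a feasibility result. This stands. What is lost under the assurance is the interview, CSQ-8 and SUS, not all information.

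**A reader might infer that the ITT analysis is contradicted.** It is not. ITT does not require outcomes from people who have withdrawn consent, and FIML under missing-at-random keeps them in the model through baseline data.

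**A reader might infer that anyone who stops the modules loses the week-8 visit.** The text does not say so. Target Population has every participant assessed at baseline and week 8, module completion and retention are separate feasibility outcomes, and the withdrawal reasons are worded as possibilities and do not name stopping the modules. The gap is only that this distinction is never spelled out.

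**A reader might claim a narrower confidence interval from better follow-up.** That needs an assumed share of leavers who would attend week 8, for which the documents give no basis, and a completers-only formula that is not the planned analysis.

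**Conclusion.** The contradiction is real and sits in the current text: the assurance and the interview plan cannot both be followed, and the interviews belong to a primary outcome. Its reach is at most about 12 of 60 participants at the planned dropout, about 6 of them in the d-DBT arm if loss is equal. Whether the result is one-sided acceptability evidence or a broken assurance depends on which statement staff follow, so neither should be presented as certain.

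The conclusion rests on reading the assurance as written and on there being no exception in the consent form. It does not extend to the ITT analysis, to people who merely stop using the programme, or to the stated precision. The point should be settled by amendment, preferably before enrolment, because what participants have been told is hard to change afterwards.

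**What to change.** Reconcile the Qualitative methods, Participant Recruitment and Screening, and Participant Withdrawal Criteria sections, and the consent form, by defining two states:

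- **(a) Stopping the d-DBT programme.** The participant stays in the study and is invited to the week-8 assessment and the interview.
- **(b) Withdrawing consent to research data collection.** No new data are collected, unless the participant has explicitly agreed to an optional interview. The assurance should state this exception in the same sentence.

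The interview plan should then name group (a) and those in (b) who gave that agreement.

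The cost is a wording amendment through the research ethics board. The week-8 visit and the interviews are already planned. A secondary benefit is that more week-8 outcomes may be observed, so the efficacy estimates lean less on missing-at-random; no gain in precision should be claimed for it.

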## Outcome Assessments

**Measures/Assessment Tools:** Demographic and medical comorbidity assessments, and current medication use will be gathered at baseline. Measures will be completed at study entry and repeated immediately post-intervention at 8-weeks. Clinician rated assessments will be completed with a trained research assistant. Any changes to medication will be recorded at intervention completion. Psychiatric diagnoses will be confirmed using the Structured Clinical Interview for DSM-5 (SCID-5) and Structured Interview for Psychosis-risk Syndromes (SIPS) at baseline. Clinical assessments will be completed at baseline and 8-weeks.

Primary outcomes:

1. Feasibility outcomes will include recruitment (60 participants), retention, and completeness of modules. Completeness of modules will be assessed using a brief survey after every module and participants will receive weekly virtual check ins to help with trouble shooting and enhance engagement. Participants’ ability to complete the clinical assessment schedule will also serve as a feasibility indicator.
2. Acceptability will be informed by the Client Satisfaction Questionnaire (CSQ-8) (66). Semi-structured interviews at the end of the intervention will also provide feasibility and acceptability data.
3. System Usability Scale (SUS) (67) - assesses whether the intervention is serviceable for its intended purpose. The SUS is a reliable tool for measuring the usability. It consists of a 10-item questionnaire with five response options for respondents; from Strongly agree to Strongly disagree.

Secondary Outcomes:

1. Global Functioning: Social and Role Scales (68).
2. Psychosis spectrum symptoms: SIPS (69); PRIME-Revised (70)
3. Mood and anxiety: The State-Trait Anxiety Inventory (71), Calgary Depression Scale for Schizophrenia (72).
4. Emotion Regulation: Brief Difficulties in Emotion Regulation Scale (DERS-16) (73).
5. Substance Use: Adolescent Alcohol and Drug Involvement Scale The Timeline Follow Back (TLFB) method for measuring quantity of cannabis, alcohol, and tobacco use in the past 7 days (74); The Cannabis Use Disorders Identification Test-Revised (CUDIT-R) (75);Daily Sessions, Frequency, Age of Onset and Quantity of Cannabis Use Inventory (DFAQ-CU) (76)
6. Borderline personality dimensions: BSL-23 (77).
7. Resiliency: Connor-Davidson Resilience Scale; CD-RISC (78).
8. Suicidal ideation: Columbia-Suicide Severity Rating Scale (79).
9. Cognition: The MATRICS Consensus Cognitive Battery (MCCB) (80)

**Fidelity**

d-DBT will be delivered virtually in a self-led program. This eliminates the concern of inter-practitioner variability in delivering psychotherapy. There will be weekly check-ins with our research staff who will act as ‘digital navigators’ and provide non-clinical support around application use which may include application troubleshooting, guidance through application exercises, reminders, and encouragement to support engagement (81). They will have a semi-structured script which will explore if participants have been able to complete modules, explore barriers, and help answer basic questions about the content of the modules. We will also use the DBT ways of coping checklist to measure DBT-skills use (82).

# PARTICIPANT SELECTION AND WITHDRAWAL

## Target Population

We will recruit 60 CHR participants, with a focus on diversity across genders, ethnic origins, age, and other sociodemographic characteristics. All participants will be assessed at baseline and 8-weeks. We will recruit youth (age 16 – 29 years). The sample size was informed by published literature, which suggests 24-70 participants for pilot trials (83-85).

## Participant Recruitment and Screening

Study participants will be recruited from the Slaight Family Centre for Youth in Transition (SFCYT) via two mechanisms: 1) the Slaight centralized clinical research recruitment strategy in SFCYT where a core team of clinical research staff identify and engage all patients receiving early psychosis services in clinical research, providing streamlined triaging of patients to appropriate studies; 2) the CAMH-wide Clinical Engagement and Research Recruitment (CLEARR) infrastructure that enables early identification and engagement in research for all new patients presenting for care at CAMH.

As part of the CLEARR process, a delegated, CLEARR approved Research Coordinator/Physician will identify potential participants and notify the research team and the participant’s clinician about the participant’s eligibility to participate in the study. The clinician will then ask the participant if they would be willing to meet with a study team member about participating. Only with participants’ agreement will they be approached.

The CLEARR coordinator/physician will access personal health information (PHI) in participants’ health records to determine potentially eligible participants for the study.

In case of referrals from clinics, recruitment for the study will be initiated by the clinical team who is treating the potential study participant. The treating physician/clinical care team will not obtain consent. They may identify potential research participants and obtain verbal permission from these potential participants for a member of the research team to approach them. Potential participants who indicate an interest in hearing more about the study and provide verbal consent to be contacted will be contacted by a member of the research team who will engage them in an informed consent process.

We will also contact former research participants who participated in previous studies or are currently participating in parallel studies and agreed to hear about future research opportunities and consented to be re-contacted. To avoid cold calling, the participants will be contacted by someone from the research team that the former participant was involved with.

Research personnel will contact participants according to their preferred mode of communication (email, telephone, SMS text), which will be recorded in the pre-screening/subject log. In the case of text messaging, personnel will only contact participants to schedule or remind participants of upcoming appointments.

All patients will be given the option to participate. Participation in the study is voluntary. The decision to participate will not affect patients’ receipt of treatment or clinical services. Participants will be informed that they have the option of terminating their participation at any time, without consequence and that no new data will be collected on them.

Participants will be recruited through the Slaight Centre for Youth in Transition’s centralized recruitment process. All subjects will be pre-screened with the Slaight REB approved “pre-screen form” that is implemented across all SFCYT studies to allow for alignment and data sharing and recruitment; this data will be entered into a password protected and restricted pre-screen tracking database. We conduct case review meetings twice a week to review recruitment and to identify new patients who may be eligible for research studies. Our centralized recruitment strategy allows us to ‘triage’ and ‘group’ participants into non-competing research studies to encourage referrals among PIs.

Recruitment will also be enhanced by the Toronto Adolescent and Youth (TAY) Cohort study (PI; [name]) that is recruiting 3000 youth, and emerging adults, aged 11-24 years over 5-years. The TAY study offers rich phenotypic data and aims to investigate mechanisms of disease in young people presenting to mental health services. We expect to identify many individuals with CHR from the TAY Cohort study, where to date almost 50% of participants demonstrate clinically significant levels of psychosis spectrum symptoms.

Following provision of written informed consent, participants will be assessed for suitability for inclusion in the study based on the inclusion and exclusion criteria. If it is deemed necessary, research staff may review participants’ CAMH medical charts for scheduling purposes and/or to obtain additional information for ongoing eligibility determination and/or obtain other clinically relevant information for research purposes. We will also record information about the participant’s mental health from their charts that we are unable to obtain during their interviews. The investigator or research staff may also request information from the participant’s treating psychiatrist (CAMH) after obtaining consent for release of personal health information to determine eligibility and obtain clinically relevant information for research purposes.

Study participants will receive a small honorarium to reimburse them for the time and inconvenience incurred during participation in this study. For initial assessments, post-intervention assessments and post-intervention qualitative interviews, participants will receive up to $60 for these encounters.

